## SUMMARY

### Rationale:

Several systematic reviews have indicated that additional exercise therapy and repetitive task training have a significant effect on functional outcome after stroke. Guidelines therefore conclude that patients in a rehabilitation setting should have the opportunity to get an increase of intensity of therapy. At this moment resources in rehabilitation facilities are not sufficient to meet these recommendations. A new method could be to involve caregivers (partner, family, friends) in exercise training. Previous studies suggest that this form of exercises done with a caregiver can lead to a better functional outcome for the patient and less strain for the caregiver. A critical part will be safety, adherence of the patient and caregiver and continuing support, for which innovative e-health and structured tele-rehabilitation services could be used.

In addition, a recent meta-analysis has shown that early supported discharge with additional services in the community is beneficial for optimizing the transition from the rehabilitation setting to the home situation and is cost-effective by reducing the length of stay of inpatient services, acknowledging that inpatient rehabilitation accounted for about 44% of all care of stroke costs.

**Objective:** The primary aim of this study is to evaluate the feasibility, clinical effectiveness and cost effectiveness of a caregiver mediated exercises programme combined with e-health services (CARE4STROKE) to improve self-reported health status and reduce the length of stay and costs by allowing early supported discharge of stroke patients to their own home setting.

**Study design:** randomized controlled trial (RCT).

**Study population:** 66 stroke patients and their caregivers, admitted in several rehabilitation centers, Hospital Stroke Units and nursing homes in the Netherlands will participate in this study.

**Intervention:** Participants will be randomly allocated to either 8 weeks of the CARE4STROKE programme in addition to usual care or to 8 weeks of usual care.

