### Main study parameters/endpoints:

Primary measurements of outcome: 1) Length of Stay and 2) self-reported health-status with the Stroke Impact Scale (SIS version 3.0). Secondary outcomes for included stroke patients are EuroQol-5D (EQ-5D), the Barthel Index, Rivermead Mobility Index, Berg Balance Scale, 5 meter walking speed, 6 minute walking test, Timed Up and Go Test, the Motricity Index (leg), The Fugl-Meyer assessment (leg), Nottingham Extended Activities of Daily Living and modified Rankin Scale. In order to track the daily activity, patients will wear a wireless activity monitor on the wrist one week before and after the intervention. In addition, patients keep a

diary to record adherence to the exercise program and emerging complications. Caregiver burden will be evaluated with the Caregiver Strain Index and Carer Quality of Life Index. For patients and caregivers the Hospital Anxiety and Depression Scale, Fatigue Severity Scale, General self-efficacy scale and Personal Opinion Questionnaire for empowerment will be used. In addition each couple will use a cost diary.

**Nature and extent of the burden and risks associated with participation, benefit and group relatedness:** Participants in the intervention group get a surplus of 150 minutes of exercise training a week; Caregivers will be involved and will need to allocate time to the programme as well. Care is taken to assure safe performance of the exercises. This will be accomplished by e-health and tele-rehabilitation services and safety instructions and close guidance and coaching of a therapist. The control group will have no additional benefit or risks. Assessments will take place at baseline, after the intervention and at twelve weeks follow up. They consist of questionnaires and tests, taking approximately two hours per assessment.

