## 6. METHODS

### 6.1 Study parameters/endpoints

#### 6.1.1 Main study parameters

For the patient:

- 1) Length of Stay in the HSU, RC or NH, defined as the moment of admittance-moment of discharge. (primary outcome)
- 2) Self reported health status with the Stroke Impact Scale (SIS version 3.0) 
- 3) Quality of life, measured with the EQ-5D. 
- 4) Mobility, measured by the Rivermead mobility index (RMI) 
- 5) Independence in performing basic activities of daily living, measured by the Barthel index (BI) 
- 6) Walking ability, assessed with the 5 metre walking speed, the 6 minute walking test and the timed up and go test (TUG). 
- 7) Extended Activities of daily living, measured by the Nottingham extended ADL (NEADL). 
- 8) Functional outcome, measured by Modified Rankin Scale (MRS) dichotomised to good outcome (0-2) or poor outcome (3-6). 
- 9) Balance, assessed with the Berg Balance Scale (BBS) 
- 10) Selectivity lower extremity, assessed with the Fugl Meyer (FM) lower extremity. 
- 11) Strength of the lower limb, assessed with the Motricity Index (MI). 
- 12) The amount of daily activity, assessed with a comfortable and wireless activity monitor on the wrist.

For the caregiver:

- 13) the experienced strain of the caregiver measured by the Expanded Caregiver strain index. (CSI +) 
- 14) Quality of life, measured with the CareQOL. 

For both:

- 15) Amount of (additional) practice done by the couples in the intervention and controlgroup, this will be measured with a diary (see appendix) Problems and adverse events like falls will also be recorded in the diary
- 16) Personal Opinion Questionnaire for empowerment .

- 17) Emotional functioning, measured with the Hospital Anxiety and Depression Scale (HADS).
- 18) Fatigue, measured by the fatigue severity scale.
- 19) Self-efficacy, measured by the general self-efficacy scale.
- 20) A cost diary, comprising questions on items such as consultation with neurologists, family doctors, paramedics, re-admission to hospitals or rehabilitation centres, drug use, home care and non-professional support.

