Outcome measures will be measured at baseline prior randomization, after the eight week intervention period and again after 12 weeks (follow up) by a blinded assessor who is not involved in training. Length of stay in the rehabilitation center will be reported at discharge of the patient. Self reports in the (cost)diary will take place during the intervention. To assess the long term costs, some patients will be asked to keep the cost diary until the end of the study in 2016. These data will be obtained by the blinded assessor with telephone interviews.

In addition, at the end of the intervention, semi-structured interviews will be conducted with some patients and caregivers to collect qualitative data regarding the experience of CME.

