### 8.3 Cost-effectiveness analysis

A cost effectiveness and a cost-utility analysis will be performed The primary outcome of the trial, length of Stay, in combination with the information of the cost diary will be used in the cost effectiveness analysis. Unit costs will be taken from national sources.

In the costs utility-analysis the outcome measure is quality-adjusted life-years (QALYs) based on the Dutch tariff for the Euro(QoI).

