### 9.3 Benefits and risks assessment, group relatedness

When the CARE4STROKE programme is followed patients will have a surplus of 150 minutes of training a week. Literature shows this to be beneficial for functional outcome after stroke. Next to that caregivers will be involved and will most likely feel in control because they can help. This may lower their experienced strain.

The exercise programme can be tailor made for the patient and caregiver by the therapist. Given the experience gained in the pilot study, the intervention can be considered as safe for both patients and caregivers. The small risk of adverse events will be minimized since a therapist will judge if the caregiver can adequately assist the patient during exercises before inclusion. In addition, safety instructions are provided in the app and there is a close guidance of a therapist during the intervention period. Also instructions are described what to do in case of an adverse event. The control group will have no additional benefit or risks. Assessments will take place at baseline, after the intervention and at twelve weeks post randomisation. They consist of questionnaires and tests, taking approximately two hours per assessment.

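### Cost diaries stop at week 8 for all but an undefined group of patients, although EQ-5D runs to week 12, so a 12-week cost-utility analysis would lack the last four weeks of diary costs

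*Protocol*

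**What the plan says.** The Protocol Summary gives a cost diary to everyone: "In addition each couple will use a cost diary". Section 6.1.1 (item 20) lists its contents: medical and paramedical contacts, re-admissions, drugs, home care and informal help.

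The paragraph after that list sets the diary's duration: "Self reports in the (cost)diary will take place during the intervention". The intervention period is 8 weeks in both arms: "Participants will be randomly allocated to either 8 weeks of the CARE4STROKE programme in addition to usual care or to 8 weeks of usual care". The same paragraph then provides for later costs: "To assess the long term costs, some patients will be asked to keep the cost diary until the end of the study in 2016". The data from this extension are collected by telephone by the blinded assessor. The Protocol does not say how many patients will be asked, who picks them, or whether they will be balanced by arm or centre.

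The health outcomes run longer. Section 6.1.1 (item 3) lists "Quality of life, measured with the EQ-5D", and Section 9.3 gives the schedule: "Assessments will take place at baseline, after the intervention and at twelve weeks post randomisation". Section 6.3 also counts the 12 weeks from randomisation. Length of stay is reported for each patient at discharge, with no 8-week limit.

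Section 8.3 plans two economic analyses. The cost-effectiveness analysis combines length of stay with the cost diary. The cost-utility analysis uses QALYs from EQ-5D with the Dutch tariff. Neither has a stated time horizon.

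**The concern.** Cost-effectiveness is part of the main aim (Summary and Section 2), and Section 1 presents the study as the basis for a later phase III cost-effectiveness trial. The hypothesised route to savings is earlier discharge, by 1 day from a hospital stroke unit and 7 days from a rehabilitation centre or nursing home.

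Earlier discharge may move resource use from the ward to the home, and home care, outpatient contacts and informal help are the items that the diary is there to record. Under the plan, the inpatient saving is counted in full for everyone, while the community costs that might offset it stop being recorded at week 8 for couples outside the extension. If the arms differ in those costs after week 8, the incremental cost will be wrong by that difference.

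This is a question of data collection, so it is not one to leave to an analysis plan. Diary costs for weeks 8 to 12 that were never recorded cannot be recovered later.

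The extension does not fill the gap as written. Without a rule for who is asked, a comparison of arms within that group would not be protected by randomisation. A fixed calendar end also gives early enrollees longer follow-up than late ones.

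**Working it through.** The Protocol gives no figure to reproduce here. The check compares the collection windows.

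**Inputs**
- Diary, all couples: weeks 0 to 8 (Summary; Section 6.1.1).
- Diary, extension group: from week 8 to a calendar date in 2016 (Section 6.1.1).
- EQ-5D: weeks 0, 8 and 12 after randomisation (Sections 6.1.1, 6.3 and 9.3).
- Length of stay: admission to discharge, all patients (Section 6.1.1).
- Sample: 66 patients (Section 4.3).

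**Gap under a 12-week horizon**
- 12 − 8 = 4 weeks without diary costs.
- 4 / 12 = 33% of the period.

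**What each horizon uses.** Take the usual area under the EQ-5D curve, which is an assumption because the Protocol does not name a method. Write u0, u8 and u12 for the utilities at the three visits.
- 8-week horizon, in quality-adjusted weeks: 8 × (u0 + u8) / 2. Diary costs cover all 8 weeks, but u12 is not used.
- 12-week horizon: 8 × (u0 + u8) / 2 + 4 × (u8 + u12) / 2. The second term has no matching diary costs outside the extension group.

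So the data as planned support either an aligned analysis that drops the last EQ-5D, or a 12-week analysis with incomplete costs. They do not support a complete 12-week cost-utility analysis.

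**Extension group.** Its size is not stated. As an assumption, take 10% to 50% of 66 patients:
- 0.10 × 66 = 6.6, about 7 patients, or about 3 per arm; 66 − 7 = 59 would have no diary costs after week 8.
- 0.50 × 66 = 33 patients, or about 17 per arm; 66 − 33 = 33 would have none.

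In this group the mismatch is reversed: diary costs continue past week 12, but no EQ-5D is planned after that.

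**Sensitivity to the follow-up wording.** The Summary speaks more loosely of a twelve-week follow-up. If that meant 12 weeks after the intervention, the gap would be (20 − 8) / 20 = 60%. Sections 6.3 and 9.3 both count from randomisation, so 33% is the figure to use.

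**After the fix.** With diaries to week 12 for every couple, the gap is 12 − 12 = 0 weeks.

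**The case against.** The strongest reply is that Section 8.3 fixes no horizon. An 8-week analysis from the first two EQ-5D assessments would be aligned, and the choice of horizon may properly sit in an analysis plan that is not at hand. This stands, and it makes the 33% conditional on a 12-week horizon. It does not remove the point, because the collection schedule already rules out complete costs at 12 weeks whatever the analysis plan says.

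Second, a reader might infer that all costs after week 8 are lost. The documents do not support that. Index inpatient days are recorded to discharge for everyone. Section 7.2 records adverse events during the study and treats those requiring hospitalisation as serious, so many hospital re-admissions would be noted, though not in the detail that costing needs. Section 5.3 says that usual care is recorded during the study. The gap concerns the diary items.

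Third, the cost-effectiveness analysis uses length of stay rather than QALYs, so the mismatch between costs and QALYs belongs to the cost-utility analysis alone. This is correct. The cost-effectiveness analysis is touched only in that its diary costs also end at week 8 for couples outside the extension.

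Fourth, a reader might infer that the extension patients are hand-picked by staff or select themselves. The text states neither. It gives no rule, and it does not say that this group will be compared between arms or pooled into the incremental cost. What can be said is that selection is uncontrolled as written.

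Fifth, the general sentence on outcome timing could be read to carry the diary to week 12. The more specific diary sentence that follows limits it to the intervention, and a separate extension for only part of the sample confirms that reading.

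Last, this is a pilot, and a longer diary is a burden. That is a fair trade-off to weigh, but four weeks ending at an existing assessment is a modest addition.

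**Conclusion.** The point holds in a limited form. Following the Protocol leaves diary costs for weeks 8 to 12 uncollected for every couple outside an extension group that has no stated size or selection rule. If the cost-utility analysis uses the week-12 EQ-5D, 4 of 12 weeks lack those costs. An 8-week horizon restores alignment only by giving up the last utility measurement and any later community costs.

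The 33% is a share of time. It should not be read as a share of cost, because the Protocol contains no cost amounts. Nor do the documents support a claim that the result would favour one arm: community costs after week 8 could differ in either direction or not at all. The clinical outcomes are unaffected.

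The conclusion rests on two readings: that the 12 weeks run from randomisation, and that the specific diary sentence governs over the general one. A change is warranted because cost-effectiveness belongs to the main aim, the missing data cannot be recovered afterwards, and the remedy is small.

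**What to change.** - In Section 6.1.1, have every couple in both arms keep the cost diary from baseline to the assessment at 12 weeks after randomisation.
- In Section 8.3, name 12 weeks as the common horizon for costs and QALYs.
- Define the extension to 2016 by a fixed rule applied equally in both arms, for example all couples enrolled before a set date. Report it descriptively, stating the differing lengths of follow-up.

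The cost is four more diary weeks per couple (12 instead of 8), which can be collected at an assessment already planned. Some more missing diary data is possible. No extra visit is needed.

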### **6.1.2 Other study parameters**

Patient and caregiver characteristics will be recorded. Of the patient we will document: age, type of stroke, date of stroke, hemiplegic side, sensory deficits (yes/no), hemianopia (yes/ no) and neglect (yes/no). Of the caregiver we will record: age, relation to patient, work (yes/no), duration of partnership and existing morbidities

## **6.2 Randomisation, blinding and treatment allocation**

In this study patients will be at random to the control or the experimental group using stratified block randomisation. Patients allocated to the experimental group will receive the CARE4Stroke program. The randomisation procedure will be executed by an independent researcher. The study will be registered in the Dutch trial register.

### **6.3 Study procedures**

Every patient with stroke, admitted in one of the participating centres, will be screened for eligibility by their own treating medical specialist to evaluate if participation in this study is possible. On a registration form will be noted: if a person is asked, if this person wants to participate, and what the considerations were. An information letter is handed to patient and caregiver and a reflection period of one week will follow. Eligible patients and their chosen caregiver will be informed in an interview with the primary researcher and a therapist will judge if the caregiver can adequately assist the patient during exercises. Upon inclusion, informed consent will be signed. Thereafter the baseline measurements will be done (T0).

The couples will be randomly allocated to either the intervention or control group.

For the couples allocated to the intervention group the intervention starts directly. After eight weeks the same measurements as at baseline will be repeated (T1) for every couple. Follow up measurements will be performed 12 weeks post randomisation.

(see figure 1)

The assessments consist of clinical tests and questionnaires (see outcome measures). The assessments and inclusion will be done by an assessor who is blinded to treatment allocation.

Prior to starting the inclusion of patients, all therapists will be extensively trained in applying the CARE4STROKE programme to optimize standardization with regard to coaching the participants and performing the weekly training sessions in which patient and partner learn the exercises.

### **6.4 Withdrawal of individual subjects**

Participants can leave the study at any time for any reason if they wish to do so without any consequences. The investigator can decide to withdraw a participant from the study for urgent medical reasons. In the patient and caregiver information letter participants will be informed about their right to withdraw from the study or intervention without any explanation

### **6.5 Replacement of individual subjects after withdrawal**

Individual participants will not be replaced after withdrawal.

**6.6 Follow-up of subjects withdrawn from treatment**

If participants decide to terminate the assigned intervention premature, they will be asked if they want to continue completing the outcome measurements. They can refuse this request without any consequences.

**6.7 Premature termination of the study**

There are no specific criteria for premature termination of the study.

## 7. SAFETY REPORTING

### 7.1 Section 10 WMO event

In accordance to section 10, subsection 1, of the WMO, the investigator will inform the subjects and the reviewing accredited METC if anything occurs, on the basis of which it appears that the disadvantages of participation may be significantly greater than was foreseen in the research proposal. The study will be suspended pending further review by the accredited METC, except insofar as suspension would jeopardise the subjects' health. The investigator will take care that all subjects are kept informed.

### 7.2 Adverse and serious adverse events

Adverse events are defined as any undesirable experience occurring to a subject during the study, whether or not considered related to the experimental treatment. All adverse events reported spontaneously by the subject or observed by the investigator or his staff will be recorded.

A serious adverse event is any untoward medical occurrence or effect that at any dose:

- results in death;
- is life threatening (at the time of the event);
- requires hospitalisation or prolongation of existing inpatients' hospitalisation;
- results in persistent or significant disability or incapacity;
- is a new event of the trial likely to affect the safety of the subjects, such as an unexpected outcome of an adverse reaction, lack of efficacy of an IMP used for the treatment of a life threatening disease, major safety finding from a newly completed animal study, etc.

All SAEs will be reported through the web portal *ToetsingOnline* to the accredited METC that approved the protocol, within 15 days after the sponsor has first knowledge of the serious adverse reactions.

SAEs that result in death or are life threatening should be reported expedited. The expedited reporting will occur not later than 7 days after the responsible investigator has first knowledge of the adverse reaction. This is for a preliminary report with another 8 days for completion of the report.

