Recently, Gregory et al. recommended a crucial role of e-Health and ICT support for the coordination of caregiver-mediated interventions. However, none of the existing studies however have combined e-Health services with Caregiver Mediated Exercise to enhance Early Supported Discharge. .

The present type I cost-effectiveness study will serve as basis for a future cluster stepped-wedge randomized phase III clinical trial to investigate the cost-effectiveness of the CARE4STROKE program, in which Caregiver Mediated Exercise is combined with e-Health services aimed at Early Supported Discharge

We hypothesize that the CARE4STROKE program will:

- 1) be feasible and safe to execute;
- 2) allows ESD of patient to their own home setting with a significant reduced inpatient stay of 1 day for HSU and 7 days for RC/NH.
- 3) increase patients self-reported health status with concomitant reduced levels of caregiver burden and
- 4) enhance feelings of empowerment as perceived by patient and partner when compared to usual care..

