## 2. OBJECTIVES

The CARE4STROKE program is directed at improving self-reported health status and reduce LOS and costs by allowing ESD of stroke patients to their own home setting. ESD from setting of admission will be enhanced by: 1) starting CME applied by a PT focused on gait and gait-related activities immediately after admission in a HSU, RC NH and 2) continuous weekly support by a PT in patients own home setting after discharge with support of e-Health services. The e-Health services will contain the following package: 1) an app with CME for 8 weeks, starting immediately after admission; 2) telerehabilitation services allowing instructions of the PT including monitoring progress of patients and adherence of caregiver and 3) telephone and video conferencing based counseling and weekly visits by a coordinating PT from the setting of discharge focused on increasing feelings of empowerment and self-management of the caregiver.

The main aim of the present pilot study is to investigate feasibility, clinical effectiveness and cost-effectiveness of a caregiver-mediated exercise program (CARE4STROKE) combined with e-Health services, to be evaluated in terms of self-reported health status and mean LOS in stroke patients who are admitted at a HSU, RC or NH and discharged to their own home setting, as compared to usual care.

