## 5. TREATMENT OF SUBJECTS

### 5.1 Investigational treatment

The CARE4STROKE program consists of eight weeks of complementary exercise therapy done with a caregiver, next to the usual therapy. 31 standardized exercises are available, that can be customized per patient and caregiver into an individualized program. These exercises were devised in collaboration with movement scientists and physical therapists and were shown to be feasible in the pilot study in Reade. The exercises are presented in an E-health application (app) for a tablet. Regular reminders to exercise can be given by the app. The exercises are aimed at improving skills related to walking ability like sitting, standing and making transfers, or are supporting exercises to improve mobility, strength and balance. The patient and their caregiver are asked to do the exercises minimally 5 times a week for 30 minutes on at least both weekend days or the equivalent dosage with an adopted schedule. When the intervention is correctly performed patients will have a surplus of 150 minutes of caregiver mediated therapy a week.

Patients and their caregiver will have a weekly session with a trained therapist. In this session, the participating couple will be instructed as to which exercises should be performed safely during the next week and evaluate the exercises done last week. All patients and caregivers will be supported by a handbook with instructions.

The program starts when the patient is admitted in one of the participating centres. When the discharge date of the patient is earlier than the finishing of the program, the program continues at home with continuous monitoring from the treating therapist.

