### 5.3 Use of co intervention

All patients that receive usual care will not be enrolled in other studies. During the study, usual care will be recorded. Participants in both the intervention and control group will use a diary to register every therapy and (self) training session.

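### Section 7.2 captures adverse events passively, leaves out the both-arm diary of 6.1.1 and sets no common enquiry to week 12, while scheduled weekly programme contact exists in one arm only

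*Protocol*

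**What the plan says.** Section 7.2 defines an adverse event as any undesirable experience during the study, related or not, and gives the capture rule: "All adverse events reported spontaneously by the subject or observed by the investigator or his staff will be recorded". No scheduled enquiry is stated there, and the diary is not mentioned.

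Section 6.1.1, item 15, provides a second route. It begins "Amount of (additional) practice done by the couples in the intervention and controlgroup, this will be measured with a diary" and adds "Problems and adverse events like falls will also be recorded in the diary". Section 5.3 confirms that the diary is kept in both arms: "Participants in both the intervention and control group will use a diary to register every therapy and (self) training session". On timing, 6.1.1 says "Self reports in the (cost)diary will take place during the intervention". Only a cost diary, in some patients, continues beyond that, and falls are not among its listed items.

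Contact differs by arm. For the programme, section 5.1 says "Patients and their caregiver will have a weekly session with a trained therapist", and the programme continues at home if discharge comes before its end. Section 2 adds "telephone and video conferencing based counseling and weekly visits by a coordinating PT from the setting of discharge". Section 5.2 gives controls usual care according to guidelines, without a contact frequency. Under section 6.3 every couple is assessed at eight weeks and again at 12 weeks after randomisation.

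The first hypothesis in section 1 is that the programme will "be feasible and safe to execute".

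**The concern.** A passive rule finds more events where staff look more often. After discharge, the staff-observation route in 7.2 has a stated weekly occasion in the CARE4STROKE arm and none in the control arm. The same minor fall at home could be noted in one arm and missed in the other.

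The diary could even this out, but 7.2 does not name it as a source of adverse events. The plan therefore does not say which record a safety table is built from. Diary self-report is also tied to the intervention period, while the definition in 7.2 runs for the whole study.

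Safety is part of the first hypothesis, and falls are the event the protocol names. Section 8.2 compares the outcomes of 6.1.1 between arms, and diary-recorded falls sit in 6.1.1, so a between-arm reading is foreseeable. No analysis plan can recover events that nobody asked about, so this has to be settled in data collection.

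**Working it through.** The protocol states no adverse-event rate, safety margin or safety power, so there is no figure to reproduce. The check compares the sections and then gives an illustration.

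**1. Stated sources by period** (week 12 counted from randomisation, as in 6.3 and 9.3)

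| Source | CARE4STROKE | Usual care |
|---|---|---|
| Weeks 0–8: diary including falls (6.1.1, 5.3) | yes | yes |
| Weeks 0–8: weekly programme session, also at home (2, 5.1) | about 8 | none; usual-care contact not quantified |
| Week-8 assessment (6.3) | yes, no event question stated | yes, no event question stated |
| Weeks 8–12: diary for falls | none stated | none stated |
| Weeks 8–12: programme contact | ended | none |
| Week-12 assessment (6.3) | yes, no event question stated | yes, no event question stated |

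Trial-specific contacts after baseline: CARE4STROKE about 8 + 2 = 10; control 2, plus an unknown number under usual care.

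**2. What differs and what is shared**

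- Weeks 0–8: the diary is common to both arms, and scheduled weekly contact is not. The possible imbalance lies here.
- Weeks 8–12: diary and programme contact have both stopped. The gap is 12 − 8 = 4 weeks, 4/12 = 33% of follow-up, and is the same in both arms.

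**3. Illustration of size in weeks 0–8**

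Inputs: 66/2 = 33 patients per arm (section 4.3). Assumptions not in the protocol: the same true risk p of at least one event in both arms, and capture shares c_E (CARE4STROKE) and c_C (control).

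Recorded patients per arm = 33 × p × c. Apparent risk ratio = (p × c_E)/(p × c_C) = c_E/c_C, which does not depend on p. With p = 30%, the true number is 33 × 0.30 = 9.9 per arm.

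| c_E | c_C | Recorded, CARE4STROKE | Recorded, control | Apparent ratio |
|---|---|---|---|---|
| 100% | 100% | 9.9 | 9.9 | 1.00 |
| 100% | 90% | 9.9 | 8.9 | 1.11 |
| 90% | 70% | 8.9 | 6.9 | 1.29 |
| 90% | 50% | 8.9 | 5.0 | 1.80 |

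For the last row, p = 20% gives 5.9 against 3.3 and p = 40% gives 11.9 against 6.6, with the ratio still 1.80. Any equal pair of shares gives 1.00, which is what the both-arm diary would deliver if it were kept equally well. The table takes capture to be at least as full in the CARE4STROKE arm. If staff saw more events among controls, the ratio would fall below 1.

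**The case against.** The strongest reply is that the plan already has a common source. The diary records falls and other events in both arms over exactly the eight weeks in which contact differs, and it sits in the section whose outcomes are compared between arms. Section 7.2 leads to ethics committee notification and need not feed that comparison. The diary form is in an appendix that is not in the text at hand. Hypothesis 1 can also be read as non-comparative, because the comparison with usual care is worded only at the end of hypothesis 4.

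Much of this stands, and it rules out several stronger readings:

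- A reader of 7.2 alone might infer that events are captured only by spontaneous report or staff observation. The diary in 5.3 and 6.1.1 contradicts that.
- A reader might take the week-8 diary stop as a cause of imbalance. Programme contact ends at the same time, so the gap is shared.
- A reader might suppose that the weekly session prompts diary keeping. Section 5.1 describes instruction on and evaluation of exercises; prompting is an inference.
- A reader might expect the programme to look more harmful. Section 1 anticipates a stay shorter by 1 day (hospital stroke unit) or 7 days (rehabilitation centre or nursing home). Controls may thus spend longer where staff can see a fall, which could offset or reverse the direction.

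The reply does not remove three facts: 7.2 omits the diary, no common question is stated at either visit, and scheduled programme contact exists in one arm only. A self-completed diary may also be kept differently in the two arms.

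**Conclusion.** The concern holds as a risk of unequal ascertainment of non-serious adverse events in weeks 0 to 8, plus a separate gap in solicited falls data in weeks 8 to 12 that both arms share. Calling the arms' safety data not comparable, or a difference impossible to attribute, goes beyond the documents.

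The size is unknown. The illustrative ratio of 1.0 to 1.8 rests wholly on assumed capture shares and equal true risk, and 1.0 applies if the diary works equally. The direction is also open, because usual-care contact is unquantified and inpatient time may differ. The 4-of-12-week gap follows from the text, reading the falls diary as ending with the intervention. This is an inexpensive improvement worth making, not a defect that undermines the trial.

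**What to change.** Reconcile 7.2 with 6.1.1:

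1. In 7.2, name the both-arm diary as a source of adverse events. In 6.1.1, keep its falls and problems page in both arms until the 12-week visit.
2. At the 8-week and 12-week visits, have the blinded assessor ask every couple in both arms the same short fixed questions, after the outcome tests: falls, injuries and admissions since the last visit, for patient and caregiver.
3. Make these common sources the primary basis of any between-arm safety comparison. Still report all therapist-observed events in full, identified by source. Serious adverse event reporting stays as it is, whatever the source.

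Cost: changed wording in two sections, a few minutes at two existing visits, and four more weeks of one diary page. The downsides are some recall error and a small unblinding risk. Asking last protects that visit's tests, but unblinding at week 8 could carry over to week 12.
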